#### Potential Covariates

The following variables, measured at baseline, will be assessed as covariates:

Participant characteristics: race, Hispanic ethnicity, gender identity, biological sex, RUCC codes (4 to 9), age, education, employment, and emerging adults’ height and weight for BMI (treated as a covariate because of stability at this age) [171]Household features: marital status, parenting status (children at home), household composition, food insufficiency [149], and use of government nutrition assistance programs [155]Health care use: insurance status [172] and prior visit to a physician for routine preventive careCancer history: personal and family history of cancerCancer messaging: exposure to cancer information (ie, topics and sources [health care provider, social media, website, news media, and conversations]) [64] and perceived credibility of various media [133]Social desirability: a socially desirable response set 5-item measure [173] to account for socially favorable response bias.

#### Social Media Campaign Engagement Measures

Behavioral and experiential measures of campaign engagement [174,175] will be collected, guided by the model of engagement by Perski et al [176]. Behavioral measures will be (1) staff records of posts; (2) counts of emerging adults’ views, reactions (eg, like or sad), and comments extracted in identified format using our custom-written app and coded for content and pro, anti, or neutral sentiment by 2 trained research assistants [113]; and (3) use of resources on the project website recorded by the web server. Experiential measures will be collected in each postintervention test, including time spent and frequency of reading posts, flow experience (ie, social interaction, enjoyment, and concentration) [177], cancer information overload [178], and sharing post content with others.

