**Figure 1 figure1:**
[figure not shown]
Randomized stepped-wedge trial design.

Following baseline assessment (T_0_), emerging adults will be stratified by state, ethnicity (racial and ethnic minority individuals vs non-Hispanic White individuals), and biological sex (male vs female) and randomly assigned to 1 of 4 cohorts differing in intervention duration by the project biostatistician. All cohorts will complete postintervention assessments at weeks 13 (T_1_), 26 (T_2_), 39 (T_3_), 52 (T_4_), and 104 (T_5_). All data collection will be conducted using the secure web-based REDCap (Research Electronic Data Capture; Vanderbilt University) application. The primary outcomes measured at all assessment times will be MVPA, healthy eating patterns, nicotine product use, alcohol intake, sunburn, and HPV vaccination.

The social media campaign will be conducted over 12 months in 4 separate Facebook private groups. The intervention will start in each cohort at successive 13-week intervals, so cohorts will receive varying doses of campaign exposure (ie, 180 posts per 13-week interval) via stepped entry. Specifically, cohort 1 (250/1000, 25%) will start the social media campaign at week 1, receiving approximately 720 posts in 52 weeks. Cohort 2 (250/1000, 25%) will start the campaign at week 13 (approximately 540 posts), cohort 3 (250/1000, 25%) at week 26 (approximately 360 posts), and cohort 4 (250/1000, 25%) at week 39 (approximately 180 posts). Emerging adults will be told to read, react to, and comment on posts as often as they like. Exposure to cancer risk information and misinformation from other sources will be controlled by randomization.

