The stepped-wedge quasi-experimental design was selected because it has several methodological advantages [91]. First, it allows for the random assignment of participants to 1 of the 4 cohorts, ensuring that potential confounding factors are evenly distributed across the groups. Each cohort is assigned to start the intervention at different times, creating a staggered, time-sequenced implementation schedule across the cohorts that creates the controlled nature of our trial. This design element allows for the within-study comparison of outcomes across different cohorts, with each cohort serving as a control for the others before they receive the intervention. Specifically, the control condition is represented by the periods when the cohorts have not yet started the intervention. For example, cohort 2 serves as a control group for cohort 1 before they commence their intervention in week 13. Second, the design also allows for comparisons between cohorts that have received the intervention for different durations. Third, by collecting data at multiple time points (T_1_-T_5_), the design facilitates the assessment of outcomes over an extended period that allows for the evaluation of trends and changes in outcomes over time within each cohort as well as comparisons between cohorts. The multiple baseline measures in cohorts 2, 3, and 4 will permit the examination of any trends or patterns before the intervention is introduced and will control threats to validity [92], as we can account for potential confounding factors, such as time-related effects or external factors, and compare cohorts at different stages of intervention exposure. This strengthens the internal validity of the study. Fourth, the design optimizes study resources by focusing on recruiting and retaining a longitudinal sample. This approach differs from securing a sample where half remain untreated, mitigating problems associated with control groups such as loss to follow-up, demoralization, disengagement, or noncomparability. It adheres to ethical standards by having all participants eventually receive the intervention but still preserves the controlled trial’s integrity.

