### Cancer Prevention Social Media Campaign

The social media campaign will deliver 2 posts per day (n=approximately 720 posts) over 12 months, addressing cancer risk reduction, teaching digital and media literacy, encouraging family and friend communication, responding to misinformation, and highlighting community resources. The diverse content should be engaging and should avoid fatigue, but we will assess information overload and compare varying intervention durations (ie, 13, 26, 36, and 52 weeks).

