#### Mediators

Mediators will be assessed in all surveys. These include theoretical antecedents—cancer risk (SCT; severity and susceptibility: 6 items); self-efficacy and response efficacy (SCT) [162]; cost of cancer prevention [162]; descriptive norms (SCT; 2 items; prevalence among people you know and 5 people you know best) [163]; social support from family, friends, and partners (SCT); relatedness (SDT; 4 items) [164]; autonomy and motivation (SDT; 10-point contemplation ladder) [154,165]—family and friend communication about cancer prevention (SDT and DIT; if emerging adults shared information from feed with family and friends) [166]; and vaccine antecedents (ie, confidence, constraints, complacency, calculation, and collective responsibility [167]). Digital and media literacy will be assessed with 3 competency measures—self-perceived media literacy (4 items) [168], perceived social media literacy (6 items) [169], and eHealth literacy (8 items) [170]—along with cancer prevention misinformation (8 accurate and 8 inaccurate Likert statements recoded for belief in misinformation).

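### Cancer information overload is not measured at baseline, so cohort 1 has no unexposed value and comparisons of overload by campaign duration lose some precision, though not validity

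*Protocol article*

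**What the plan says.** In Social Media Campaign Engagement Measures, the experiential block is scheduled as follows: "Experiential measures will be collected in each postintervention test, including time spent and frequency of reading posts". The same list ends with "cancer information overload [178], and sharing post content with others". Randomized Stepped-Wedge Trial Design names T0 as the baseline, taken before randomization, and fixes the later tests for everyone: "All cohorts will complete postintervention assessments at weeks 13 (T_1_), 26 (T_2_), 39 (T_3_), 52 (T_4_), and 104 (T_5".

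Other measures are scheduled differently. The primary outcomes are placed in the T0 to T5 surveys, and for the mediators the text is "Mediators will be assessed in all surveys". Overload appears neither there nor among the baseline covariates.

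On exposure, "cohort 1 (250/1000, 25%) will start the social media campaign at week 1, receiving approximately 720 posts in 52 weeks", and then "Cohort 2 (250/1000, 25%) will start the campaign at week 13 (approximately 540 posts), cohort 3 (250/1000, 25%) at week 26"; cohort 4 follows at week 39. The section on the campaign itself gives overload a purpose, as a check on fatigue: "we will assess information overload and compare varying intervention durations (ie, 13, 26, 36, and 52 weeks".

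**The concern.** Overload is the article's stated safeguard against two posts a day for a year being too much. A scale about cancer information in general can be answered before any campaign post has been seen, unlike items on time spent reading posts or sharing them. On the stated schedule, cohorts 2 to 4 are in fact asked it before their campaign starts (if the survey comes first in a shared week). Nothing in the schedule therefore prevents asking it at T0.

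Leaving it out has two direct consequences. Cohort 1, with the longest campaign and about 720 posts, supplies only exposed values, so its change from before the campaign is unknown. And no cohort has a pre-randomization value with which to check balance on overload or reduce residual variance. The open question is how much this costs any comparison of overload across durations.

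**Working it through.** The article states no figure for overload, so there is none to reproduce. The check has three steps.

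**1. Exposure at each overload measurement.** Campaign weeks received, from the start weeks in the trial design section:

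| Cohort | T0 | T1 | T2 | T3 | T4 |
|---|---|---|---|---|---|
| 1 | not asked | 13 | 26 | 39 | 52 |
| 2 | not asked | 0 | 13 | 26 | 39 |
| 3 | not asked | 0 | 0 | 13 | 26 |
| 4 | not asked | 0 | 0 | 0 | 13 |

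Cohort 1 has no zero. The zeros at weeks 13, 26 and 39 for the cohort starting in that week assume that the survey precedes the start; the article does not state the order. The table uses 39 weeks, which follows from the start weeks. The campaign section prints 36, and the two should be reconciled.

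**2. Are duration effects still estimable without T0?** The model is the one described for the primary outcomes: a person random intercept, categorical calendar time and categorical exposure time. Applying it to overload is an assumption. Inputs are 175 per cohort and correlation ρ = 0.5 (both from Power Analysis; ρ is not an overload value, so 0.3 and 0.7 are also shown), with SD 1. T5 is left out of both versions.

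- V = (1 − ρ)I + ρJ, where J is a matrix of ones
- Information = Σ over cohorts of 175 · A′V⁻¹A, where A is the cohort's design matrix
- SE = square root of the relevant element, or contrast, of the inverse

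With T0 there are 5 calendar and 4 exposure parameters, rank 9 of 9. Without T0 there are 4 + 4, rank 8 of 8. All four duration effects remain estimable.

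**3. Precision lost (SE in SD units).**

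| Contrast | ρ | With T0 | Without T0 | Ratio |
|---|---|---|---|---|
| 52 weeks vs unexposed | 0.3 | 0.1083 | 0.1155 | 1.07 |
| | 0.5 | 0.1005 | 0.1158 | 1.15 |
| | 0.7 | 0.0833 | 0.1052 | 1.26 |
| 52 vs 13 weeks | 0.3 | 0.0915 | 0.0954 | 1.04 |
| | 0.5 | 0.0823 | 0.0908 | 1.10 |
| | 0.7 | 0.0668 | 0.0794 | 1.19 |

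With a single on/off treatment effect at ρ = 0.5, the SE goes from 0.0414 to 0.0436, a ratio of 1.05.

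A simpler cross-check compares cohort 1 with cohort 4 at week 52. Without baseline, SE = √(2/175) = 0.107. With adjustment for T0, SE = 0.107 × √(1 − 0.5²) = 0.093. At 80% power and two-sided 0.05 (assumed), the detectable difference is 0.107 × 2.80 = 0.30 SD without T0 and 0.093 × 2.80 = 0.26 SD with it.

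**The case against.** The strongest reply is that the comparison of durations never needed a baseline. Cohorts are assigned at random, and the article locates the control elsewhere: "the control condition is represented by the periods when the cohorts have not yet started the intervention". At week 52 the four durations can be set side by side directly, and cohorts not yet started supply concurrent unexposed values before then. This stands. A reader might infer from the missing T0 that the overload comparison by duration is invalid or cannot be made; the documents do not support that.

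Second, the sentence in the campaign section can be read as two separate acts: assess overload, and compare durations on the risk behaviors. The analysis section relates experiential engagement and campaign duration to risk behaviors, and it specifies the calendar-time and exposure-time model only for the primary outcomes. This also stands, so the figures above are conditional on overload being analysed as an outcome by duration.

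Third, overload is in neither hypothesis, nor in Table 1, nor among the mediators, and placing it with the other reactions to the feed is coherent. That limits the priority. It does not remove the gap. The baseline covariates on exposure to cancer information and credibility of media are related to overload but do not measure it.

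**Conclusion.** The point holds as a minor one. As scheduled, overload has no T0 value in any cohort and no unexposed value in cohort 1. Within-person change in cohort 1 cannot be estimated, and adjustment for baseline overload is impossible throughout.

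Comparisons by duration stay unbiased and estimable but are less precise: about 15% on the SE for 52 weeks versus unexposed and about 10% for 52 versus 13 weeks, at an assumed correlation of 0.5, 175 per cohort and the primary-outcome model. Across correlations 0.3 to 0.7 the ranges are 7% to 26% and 4% to 19%.

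Squaring the first ratio gives a variance ratio of 1.33, and 1 − 1/1.33 = 0.25, so a reader might infer that a quarter of the sample is wasted. That describes one contrast under a model the plan does not assign to overload. It does not describe the trial, and no primary result is affected.

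**What to change.** Ask the general cancer information overload scale at T0 as well as T1 to T5, and use the T0 value in any analysis of overload. Keep the post-specific items (reading time, flow, sharing) in the surveys after a cohort's campaign has started. State whether each survey precedes a campaign start falling in the same week.

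The cost is a few more baseline items and a one-line change to the measures section, with no added participants, visits or staff; the downside is a slightly longer baseline survey. The article describes the trial as in start-up with measures still being piloted, when this change is easy to make. A T0 value cannot be recovered once the campaign has begun.

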### Statistical Analysis Plan

#### Hypothesis Testing

We plan to use advanced statistical methods suitable for stepped-wedge designs to compare outcomes between different cohorts and time points, which will account for both time effects and intervention effects. This includes using mixed-effects models or generalized estimating equations that can adjust for time-related trends and cohort effects. In addition, by comparing cohorts that start the intervention at different times, we will isolate the effect of our campaign from other external factors and assess whether changes in the cancer risk behaviors are more pronounced or accelerated following the introduction of our intervention compared with the periods before the intervention. In addition, our analysis will adjust for potential confounding factors that might influence cancer risk behaviors, such as age, sex, ethnicity, and other relevant sociodemographic factors. This approach ensures that the control aspects of the design are rigorously analyzed.

Specifically, the 2 hypotheses and exploratory research questions will be tested using R (R Foundation for Statistical Computing) [179] and Mplus, V8.2 (Munthén & Munthén) [180], a structural equation modeling program that allows for growth models and latent constructs (to model measurement error appropriately), repeated measures, direct and indirect effects, and moderators using interaction terms and multiple group analysis [181]. Mplus will handle missing data via full information maximum likelihood. All tests will be intent to treat. To mitigate false discovery (type I error), an α of .008 will be used (ie, the traditional α=.05÷6 [number of cancer risk factors considered]) [182]. Once the full sample is recruited, baseline data will be described and plotted, measurement models will be assessed, and transformations for normality will be examined and applied.

The effect of the treatment on each of the primary outcomes will be examined using a linear mixed-effects model for a stepped-wedge design, as outlined by Hussey and Hughes [183] and Li et al [184]. Repeated measures (6 per individual—T_0_, T_1_, T_2_, T_3_, T_4_, and T_5_ in Figure 1) will be regressed on time since the start of the study (“calendar time”) and time since the start of message exposure (“exposure time”), both of which are expressed as categorical variables via dummy codes. Any mediators found to be significantly impacted by the treatment will be subsequently examined as mediators of the treatment effect on the outcomes via formal mediation models. Multilevel mediation models will be fit as described by Preacher [185] using the structural equation modeling program. As moderation tests require a vastly larger sample than tests of main effects [186], we will examine them without conducting null hypothesis significance tests [187]. We will estimate each model, evaluate the effect magnitude as a function of the moderator, construct bootstrap CIs to illustrate uncertainty, and use false discovery rate controls [182,187]. Linear mixed-effects models for hypothesis 1 will be extended to consider effect modification because of cancer risk behaviors, campaign exposure variables, biological sex, and the time of year of data collection (to control for seasonal fluctuations in UV levels, food availability, and alcohol intake).

Finally, behavioral and experiential engagement will be tested for campaign dose response (ie, duration of the campaign) related to cancer risk behaviors. In addition, behavioral engagement with posts (ie, views, reactions, and comments) on certain topics (eg, risk behaviors, media literacy, or family communication) and formats (eg, text, video, or interactive features such as polls) will be examined to determine if they have an impact on campaign effectiveness.

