### Objectives

Our proposed intervention will aim to aid rural emerging adults in making informed decisions to reduce cancer risks related to infrequent physical activity, unhealthy diet, alcohol intake (per 2020 American Cancer Society guidelines [6]), nicotine product use, UV exposure, and lack of HPV vaccination uptake. In addition, it will help them critically evaluate and resist misinformation and marketing that promote cancer and other health risk behaviors and support emerging adults to be media literate when using digital media. The trial will test the following hypotheses:

Hypothesis 1: emerging adults will increase MVPA and healthy eating patterns, reduce nicotine product and alcohol use and sunburns, and increase HPV vaccine uptake from baseline to final assessment when receiving the social media intervention.Hypothesis 2: the positive impact of the social media campaign on cancer risk factors among emerging adults will be mediated by improved cancer risk knowledge and beliefs (ie, self-efficacy and response efficacy, norms, social support, and vaccine antecedents), digital and media literacy skills, misinformation identification, and family communication.

Analyses will also explore whether the impact of the campaign differs according to (1) the level of emerging adults’ engagement with it, (2) cancer risk factors, and (3) the biological sex of the participants. The prospective randomized quasi-experimental design and its large sample will provide a rigorous evaluation of the social media campaign compared with many previous studies on social media that have used less rigorous nonrandomized controlled trial designs and small samples [81-86].

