#### Power Analysis

To determine the appropriate sample size for the stepped-wedge design, we used the Shiny Cluster Randomized Trial calculator [188], setting α at .008 and assuming, conservatively, that the within-person correlation of the repeated measures is 0.5. Power analysis focused on the main effect on outcomes at the 104-week posttest score being significantly better than preintervention scores (ie, the time-averaged intervention effect). We considered a mean standardized difference between pre- and postexposure measure of 0.2 for a continuous outcome and a difference in pre- versus postexposure prevalence of 0.40 versus 0.48 for a binary outcome. These are conservative and relatively small effects based on our past assessment of a social media campaign [166,189] and the expectation that emerging adults are unlikely to see all posts. We will achieve a power of 0.80 with 115 people per cohort for a continuous outcome and 175 per cohort for a binary outcome. We have planned for a 30% (300/1000) dropout rate, so we will enroll 1000 emerging adult participants and expect to finish the trial with approximately 175 individuals in each cohort. We will use full information maximum likelihood methods for estimation; thus, even incomplete cases will be retained.

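### The six primary outcomes are tested at a fixed .05/6, although Holm's step-down gives the same familywise guarantee and never rejects less

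*Protocol article*

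**What the plan says.** The article's Hypothesis Testing section sets the multiplicity rule: "an α of .008 will be used (ie, the traditional α=.05÷6 [number of cancer risk factors considered"). The paragraph following Figure 1 names the family: "The primary outcomes measured at all assessment times will be MVPA, healthy eating patterns, nicotine product use, alcohol intake, sunburn, and HPV vaccination". The Power Analysis section sizes the trial at the same level, "setting α at .008", and reports 0.80 power with 115 people per cohort for a continuous outcome and 175 for a binary one, with about 175 per cohort expected to finish.

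No stepwise or gatekeeping rule is given for the primary outcomes. False discovery rate control is mentioned only for the moderation analyses. No reason is given for a single-step rule, and no simultaneous confidence intervals that would call for one are planned for the primary effects.

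**The concern.** A single-step Bonferroni cut holds every outcome to the strictest threshold even after other outcomes have been rejected. Holm's procedure orders the six p-values and compares them in turn with .05/6, .05/5, .05/4, .05/3, .05/2 and .05, stopping at the first failure. Its first step is the Bonferroni threshold, so nothing is given up. Its error guarantee is the same and needs no assumption about how the outcomes are correlated.

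The loss grows with the number of real effects. Hypothesis 1 predicts change on every outcome: "emerging adults will increase MVPA and healthy eating patterns, reduce nicotine product and alcohol use and sunburns, and increase HPV vaccine uptake". If that is even partly true, the plan as written has less chance of confirming each behaviour, and much less of confirming several together, with no stronger familywise guarantee in return.

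**Working it through.** **1. The plan's own figure.** .05/6 = .00833, printed as .008. The total is 6 × .008 = .048, so familywise error is controlled. The stated cut reproduces.

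**2. Inputs.** Six outcomes, α = .008 and power 0.80 come from the article. Two assumptions are added: tests are two-sided (sidedness is not stated), and the six test statistics are independent or equally correlated at 0.3 (no correlation between outcomes is given).

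**3. Noncentrality.** The two-sided .008 critical value is 2.652. Power of 0.80 needs a mean z of 2.652 + 0.842 = 3.494.

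**4. Thresholds.** Fixed rule: .008 throughout. Holm: .00833, .0100, .0125, .0167, .0250, .0500.

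**5. Simulation.** 400,000 vectors of six z-statistics, with mean 3.494 for real effects and 0 for nulls. Average power per real outcome, independent outcomes:

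| Real effects | Fixed .008 | Holm |
|---|---|---|
| 1 | 0.80 | 0.80 |
| 2 | 0.80 | 0.82 |
| 3 | 0.80 | 0.83 |
| 4 | 0.80 | 0.85 |
| 5 | 0.80 | 0.88 |
| 6 | 0.80 | 0.91 |

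At correlation 0.3 with six real effects, Holm gives 0.90.

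Chance of confirming all six when all are real:

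| Correlation | Fixed .008 | Holm |
|---|---|---|
| 0 | 0.26 (0.80⁶ = 0.262) | 0.66 |
| 0.3 | 0.39 | 0.71 |

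Only a small part of this comes from rounding .00833 down to .008. A fixed cut at exactly .05/6 gives 0.804 per outcome and 0.27 for all six under independence.

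If true power is 0.50 per outcome, Holm gives 0.61 with six real, independent effects.

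**6. Error control.** Holm's simulated familywise error was at or below .0486 in these configurations. Its limit of .05 is reached when five effects are overwhelming and one is null (simulated 0.050). No fixed-cut rejection was lost.

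**7. Unequal power from the article's own sample sizes.** Take 115 and 175 per cohort at face value. A continuous outcome with 175 per cohort then has mean z of 3.494 × √(175/115) = 4.310, and power at .008 of Φ(4.310 − 2.652) = 0.95. Suppose four outcomes are continuous and two binary (an assumption from Table 1), and all six are real:

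| Quantity | Fixed .008 | Holm |
|---|---|---|
| Each binary outcome, independent | 0.80 | 0.93 |
| Average over six, independent | 0.90 | 0.97 |
| All six confirmed, independent | 0.52 (0.951⁴ × 0.80²) | 0.84 |

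The continuous outcomes tend to be rejected first and release alpha to the binary ones, so the least-powered outcomes gain most.

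**The case against.** The best defence is that nothing here is wrong. The cut is valid, common and prespecified, and the trial is sized at that same level, so no outcome falls short of its planned power. That stands: the point concerns efficiency, not validity.

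Second, the size depends on the scenario. The chance of at least one rejection is the same under Holm and a cut at .05/6, and the gain with a single real effect is about 0.1 percentage point. If continuous outcomes have 0.95 power, the gain is also small when only a few of them change: 0.951 against 0.965 for three and 0.951 against 0.958 for two, independent outcomes. The all-six figures matter most if joint confirmation is wanted, and the article does not make that a success criterion. These limits are fair and belong beside the headline figures. They do not favour the fixed cut, which does better in no scenario.

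Third, a single-step cut keeps each verdict independent of the others and gives matching simultaneous intervals. That is a real convenience, but the article plans no such intervals for the primary effects.

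Fourth, the article does not reduce each risk factor to one p-value: Table 1 lists five intakes for diet and two metrics for alcohol, and exposure time is dummy coded. This is true, and it affects the plan's own division by six just as much as Holm.

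**Conclusion.** The concern holds. The fixed .008 is valid but dominated: Holm on the same six p-values gives the same .05 familywise guarantee and rejects at least as much.

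At the planned 0.80 power per outcome, under independence, the gain per real outcome runs from about 0.1 percentage point with one real effect to 11 points with six. For confirming all six, it is 0.26 to 0.66, or 0.39 to 0.71 at correlation 0.3. If continuous outcomes have about 0.95 power, the starting point is better but a clear gain remains with all six real.

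The sizes rest on two-sided tests, the assumed correlations and the article's power statement taken as given. The dominance of Holm rests on none of these. It should be changed, because the fix is nearly free and Hypothesis 1 describes the setting in which the fixed cut loses most.

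**What to change.** Replace the sentence that sets .008 with: *The six primary p-values, one per cancer risk factor, will be tested with the Holm step-down procedure at a familywise two-sided alpha of .05.* State which single test supplies the p-value for each risk factor; the division by six already needs this.

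Keep .008 in the sample-size calculation, where it stands for Holm's first and strictest step. Report Bonferroni simultaneous intervals beside the Holm-adjusted p-values.

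The cost is a short wording change, with no effect on sample size, data collection or participant burden. The one downside is that the intervals will be slightly wider than the Holm decisions imply, so an outcome can be rejected while its interval still includes no effect; a note in the report can say so. The article describes the trial as in start-up, with its statistical subcommittee still to be formed. The change can be prespecified provided outcome data have not been examined.
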